### Environmental characteristics

The relevance of country and type of ward for quality of life has already been discussed. Group size is an important factor from the micro-environment, because wards can vary in the number of residents (between six and 27), and nursing staff is an important factor, because staffing levels and education level can differ. At T0 country (the Netherlands or Belgium), type of ward (small-scale or traditional), group size (between six and 27) and nursing staff (staffing levels of qualified nurses and of other assistant staff) are recorded.

### Basic personal characteristics

#### Demographic data

As regards the basic personal data of the residents, their age and sex will be recorded at T0.

#### Cognitive decline

To provide an indication of the level of cognitive impairment, cognitive decline is included in the conceptual model. Cognitive decline has been shown to correlate with factors that are important for the quality of life, such as the occurrence and severity of problematic behaviours [33] and activities of daily living [34].

The Standardized Mini Mental State Examination (S-MMSE) measures the cognitive decline of the elderly person as the dementia progresses. In order to diagnose the severity of the influence of the disease on cognition and motor skills, the elderly person with dementia is asked to answer a series of 11 questions. For example, the resident is asked where he or she is, why they are there, what day of the month it is, to remember some words, write a sentence, copy a drawing and perform a few tasks (closing eyes/folding paper). The maximum possible test score is 30 [54]. The scale has been validated using psychometric analyses, with the conclusion that the S-MMSE is a reliable instrument and a valuable tool for assessing cognitive function [55]. The scale has a cut-off value of 27 for highly educated persons and 24 for lower-educated individuals [56].

#### Weight

Body weight can be considered as a general measure of health status. It is known that many persons with dementia begin to lose weight shortly after the onset of the disease due to a variety of physiological, psychological, medical and environmental factors [57,58]. Moreover, the literature shows that changes in the environment may improve nutritional intake [57]. This factor is therefore considered to be of relevance for this study and the most recent weight of the resident in kilograms, fully clothed and with shoes on, is taken from the personal records of the resident.

#### Activities of Daily Living (ADL)

Activities of daily living (ADL) may be considered as an indication of functional status. The literature shows that fostering ADL independence has a positive effect on the quality of life of persons with dementia [35,36].

ADL can be measured using the Barthel Index, which includes ten basic activities of daily living, namely personal hygiene, using the toilet, getting dressed, walking up and down stairs, bathing, mobility, (in)continence, requiring assistance in transferring from bed to chair, and requiring assistance with feeding. The scale is completed by a nurse or nursing assistant working in the facility who is familiar with the resident, and takes about five minutes. A score of 0 to 2 or 0 to 3 is recorded for each activity. The maximum possible score is 20. A score of 0 to 4 = Completely dependent on others; 5 to 9 = Requires lots of help; 10 to14 = Needs help but can do things alone, 15 to 19 = Reasonably independent, and 20 = Completely ADL-independent [59]. The Barthel Index is a valid and reliable measure [60].

### Behavioural characteristics

#### Behavioural problems

Behavioural problems, such as delusions, hallucinations, agitation, depression, anxiety, elation, apathy, disinhibition, irritability, aberrant motor behaviour, sleep problems and eating disorders are frequently seen in elderly people with dementia. Studies report that on average, mild to severe behavioural problems occur in 64% of cases of dementia [39], and that between 80% [40] and 90% [41] of all elderly people with dementia will develop at least one symptom of behavioural problems during the entire course of their disease. These problems cause distress and influence the quality of life not just of the elderly person concerned, but also of their family and professional caregivers [42].

The Neuropsychiatric Inventory - Nursing Home version (NPI-NH) questionnaire can be used by an independent psychologist to interview a nurse or nursing assistant working in the facility, who is familiar with the resident, about possible neuropsychiatric symptoms from which an elderly person is suffering. These symptoms include delusions, hallucinations, agitation/aggression, phobia, uninhibited behaviour, depression/dysphoria, euphoria, apathy/indifference, neuroticism, aimless repetitive behaviour, eating disorders and sleeping disorders. The NPI-NH gives an insight into the severity (1 to 3), frequency (1 to 4) and workload (0 to 5) of each of the separate behavioural disorders [61]. A total NPI-NH score can be calculated by adding together all twelve component scores (which are the product of the frequency and severity scores) [62]. Administering the questionnaire generally takes about 15 minutes. The psychometric properties and factor structure of the NPI-NH have been assessed, showing internal consistency, reliability, convergent validity and discriminant validity [63].

#### Depression

People with dementia often suffer from depressive symptoms, such as sadness, lack of energy, low reactivity to pleasant events and multiple physical complaints [43,44]. These depressive symptoms have been shown to correlate negatively with quality of life [45].

The Cornell Scale for Depression in Dementia (CSDD) was developed specifically for identifying depressive symptoms in elderly people with dementia [43]. The CSDD incorporates mood, behavioural disorders, physical characteristics of depression and cyclical functions and disorders in cognitive content. A nurse observes the elderly person and fills in an observational scale (containing 19 items and ranging from: a = cannot be judged, 0 = absent, 1 = mild, 2 = severe). The item scores are added together. Scores above 10 indicate a probable major depression. Scores above 18 indicate a definite major depression. Scores below six are generally associated with absence of significant depressive symptoms [43]. The CSDD has been assessed as a valid screening tool for depression in the elderly, being equally valid in populations with and without dementia [64].

### Behavioural interventions

#### Use of restraints

The use of restraints, including physical restraints (belts), is common practice in the long-term care setting [46,47]. Since these measures are not always effective and have other known negative physical, psychological and social consequences, their usage will influence quality of life [46,47]. Therefore, the number and type of restraints used by the resident are recorded. The range of restrictive measures includes fixation with belts, such as a large bed belt, a small bed belt, a fastening belt in a chair or wheelchair, securing the person to the bed with a blanket, using an adjustable tabletop in chair, restraining of limbs and the use of bedrails, but also the application of technological restraints such as movement detection mats or movement detection sensors in the bedroom.

#### Use of psychotropic medication

The use of psychotropic medication is common among residents with dementia in long-term care settings. It is known that the use of this type of medication may have a detrimental effect on quality of life [48-50]. The use and number of sedatives, antidepressants and antipsychotics is taken from the actual medication file in the personal notes of the resident.

### Social interaction

#### Social engagement

Participation in joint activities, such as drinking coffee together, active or passive participation in a game or taking a walk together, is related to a higher quality of life [51], while activities such as interacting with a pet and making music as part of a group have been shown to provide positive cognitive stimulation in persons with dementia [6].

The Revised Index for Social Engagement (RISE) measures the social involvement of elderly residents suffering from dementia with other residents, professional caregivers and relatives. The scale contains eight questions about the social interaction of the resident. A nurse or nursing assistant who is familiar with the resident completes the questions by marking whether or not the specific social situation mentioned in the question has occurred over the last seven days. Completing the questionnaire takes about five minutes. RISE is one of the scales derived from the larger instrument Resident Assessment Instrument 2.0 (RAI 2.0) [65]. The RAI 2.0 is used to assess a variety of factors related to the functioning of elderly residents in care homes [66]. The reliability and validity of the RISE has been assessed individually and it was found to be a valuable and stable measure for assessing social engagement in nursing homes [67], including patients with cognitive impairments [65]. The scale does not have an established cut-off value.

#### Visiting frequency of relatives

The relationship with relatives is important for residents with dementia, because this relationship may have a positive influence on the behavioural and psychological symptoms of the disease [68,69]. A nurse or nursing assistant who is familiar with the resident will record whether the resident has visitors: almost every day, once or twice a week, once every two weeks, once a month or less than once a month.

## Analyses

Comparisons will be made in the analysis to explore whether there are differences in the combination of elements that influence the quality of life of residents living in a long-term traditional or small-scale setting in the Netherlands and in Belgium.

To enable comparison of quality of life in the two countries and in both types of wards, the comparative analyses shown in Figure 2 will be central. The two types of settings will be compared within each country. Additionally, the Dutch small-scale living facilities will be compared with their Belgian counterparts. The same comparison will be made for the traditional wards in both countries.

**Figure 2 F2:**
[figure not shown]
**Comparisons**.

To make a comparison, the data will be analyzed using descriptive, quantitative and qualitative analyses. The quantitative analyses will include cross-sectional and longitudinal analyses using SAS 9.2.1^©^. The null hypothesis that 'the patterns of change in the mean response over time on the Qualidem subscales are the same in both types of long-term care settings' will be tested. The qualitative analyses will be carried out using Qualitative Comparative Analysis using TOSMANA^© ^[70]. One of the general advantages of QCA is that it combines the strength of qualitative research (within-case knowledge) with the strength of quantitative enquiry (cross-case comparison) [71]. The most conventional and intuitive type of QCA analysis will be employed for the analyses: crisp-set Qualitative Comparative Analysis (csQCA). In csQCA, a dichotomous data table will be built, based on within-case knowledge, and from this dichotomous data table a set of necessary and sufficient conditions leading to a certain outcome will be deduced [72].

This approach integrates key strengths of both qualitative (case-oriented) and quantitative (variable-oriented) methods and allows triangulation. It provides a double check to ensure that valid results are obtained despite the relatively small number of participants.

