The aim of this study is to contribute to the knowledge about the effects of small-scale living on the quality of life of residents with dementia by answering the following main research question: Which (combination of) changes in elements affects (different dimensions of) the quality of life of elderly residents with dementia in long-term care settings over the course of one year?

The relevant elements taken into account in this study are country (the Netherlands or Belgium), type of ward (traditional or small-scale), group size, nursing staff, age, sex, cognitive decline, weight, activities of daily living (ADL), behavioural problems, depression, use of restraints, use of psychotropic medication, social engagement and visiting frequency of relatives.

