### Sample size considerations

Sample size calculations are conducted for two groups (small-scale and traditional living) based on the primary outcome measure for residents, quality of life, as measured by the QUALIDEM [24]. Using an effect size of 0.50, a two-sided significance level α of 0.05 and a power of 80%, about 70 participants are needed in each group. Expecting an average drop-out rate of 20%, we aim to include about 180 residents. From the five long-term care settings that were selected for this study, 179 residents can be included.

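### Crisp-set QCA on the same residents and ratings cannot ensure valid results in a small sample, as the Analyses section claims, and it becomes less discriminating as conditions are added

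*Protocol article*

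**What the plan says.** The main research question (Background) asks which combination of changes in elements affects quality of life over one year. The list that follows begins "The relevant elements taken into account in this study are country (the Netherlands or Belgium), type of ward (traditional or small-scale), group size" and runs to 15 elements.

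The Analyses section plans cross-sectional and longitudinal quantitative analyses, with a hypothesis test on patterns of change in the QUALIDEM subscales. It adds csQCA, in which "a dichotomous data table will be built, based on within-case knowledge", and necessary and sufficient conditions for an outcome are deduced from that table. The section closes by saying that the approach allows triangulation, and then: "It provides a double check to ensure that valid results are obtained despite the relatively small number of participants".

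The article does not say how many of the 15 elements, or which, enter the csQCA. Sample size considerations and Table 1 give 179 residents at T0 and an expected drop-out of 20%.

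**The concern.** The closing sentence is a positive claim about what the method achieves, not a detail left for later. It fails in two ways.

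- **It is not an independent check.** The csQCA has no sample of its own. Both analyses use the residents of Table 1 and, for the most part, instruments completed by or through the same nurses and nursing assistants. The Discussion concedes that the study is not randomised and that the wards are not entirely comparable. Dichotomising the same data and reading it again leaves confounding, rating error and chance imbalance where they were. csQCA also carries no error rate of its own.
- **Small numbers are a weakness of csQCA, not something it cures.** As conditions are added, residents spread over more rows. Rows with one or two residents rarely contradict themselves, so they look sufficient even when nothing is related to the outcome.

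What is at stake is the inference from agreement. If the two analyses agree, the article's wording would let that be reported as validation of the answer to the main research question.

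**Working it through.** **Inputs from the documents**
- Residents: Table 1, 98 + 81 = 179. After 20% drop-out: 0.8 × 179 = 143.2, about 143.
- Elements: 15, by count of the list in Background. Four are environmental and recorded once, at ward or setting level (country, type of ward, group size, nursing staff). That leaves 11 resident-level elements. Removing age and sex, which Table 2 records only at T0, leaves 9 measured three times.

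**The plan's own sample-size figure.** For effect size 0.50, two-sided α 0.05 and 80% power, the normal formula gives 2 × (1.960 + 0.842)² / 0.50² = 62.8, so 63 per group; the t-test gives 64. The article says "about 70 participants are needed in each group", which is on the safe side. Then 140 / 0.8 = 175, close to its target of about 180. This figure concerns the two-group comparison and does not bear on csQCA.

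**Row count.** With k dichotomous conditions there are 2^k rows.
- k = 15: 32,768 rows; 179 / 32,768 = 0.55% can be occupied at most (143 residents: 0.44%).
- This is nominal. If the four environmental elements are fixed by the six setting-by-ward-type cells of Table 1 (an assumption), 6 × 2^11 = 12,288 rows are reachable.
- k = 9: 512. k = 5: 32. k = 4: 16.

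**How often pure noise looks consistent.** Take an outcome unrelated to every condition and present in half the residents. A resident sits in a contradiction-free row if no other resident shares that row with the opposite outcome. For independent conditions with prevalence 50%, the expected share is (1 − 0.5/2^k)^(N−1):
- k = 15, N = 143: (1 − 1/65,536)^142 = 0.998
- k = 9, N = 143: (1 − 1/1,024)^142 = 0.87
- k = 5, N = 143: (1 − 1/64)^142 = 0.11
- k = 4, N = 143: (1 − 1/32)^142 = 0.01

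Simulation confirms these and extends them to prevalence 30%. Ranges below cover prevalence 30–50% with independent conditions:

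| Conditions k | N = 179 | N = 143 |
|---|---|---|
| 15 | 97.6–99.8% | 98–99.8% |
| 9 | 62–84% | 67–87% |
| 5 | 6–8% | about 11% |
| 4 | 0.4–2.3% | 1–4% |

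**More realistic structure for all 15.** With four setting-level and 11 resident-level conditions, 143 residents, prevalence 30–50% and correlation 0–0.3, 79–99% of residents are alone in their row and 84–99% are in contradiction-free rows. A harder test (six cells, 179 residents, prevalence 20–50%, latent correlation 0.2–0.6) still gives 53–98%.

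**Two limits on the small-k figures**
- They assume the outcome splits evenly. If only 20% have it, the k = 5, N = 143 figure becomes 0.8 × (1 − 0.2/32)^142 + 0.2 × (1 − 0.8/32)^142 = 0.33.
- They use the full sample. The Analyses section makes comparisons within each country central, and Belgium has 47 + 30 = 77 residents. At N = 77, with an even split, five conditions give 22–30%.

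**The case against.** The strongest reply is that the article never says all 15 elements enter the csQCA. The list belongs to the conceptual model, and choosing conditions is a detail that a full protocol or analysis plan may hold. This stands. A reader might infer that the csQCA as planned fits pure noise and cannot fail. The documents do not support that: it is severe from about eight conditions upward and slight at four or five in the full sample. The missing number of conditions is not raised here as an omission. It matters only because nothing in the text backs the assurance.

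A reader might also infer that cut-points will be chosen to suit the outcome, or that csQCA is undermined because RISE has no established cut-off and the quoted S-MMSE thresholds depend on education. These do not hold either. The article describes how the table is built without saying that QUALIDEM results are seen first. A scale without an established cut-off can still be dichotomised. Nothing says the S-MMSE thresholds will be used in the csQCA.

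It can further be said that the stated hypothesis test is quantitative, and that the Analyses section opens by describing the comparison of combinations as exploratory. Both are true and limit the harm. A second method can also show that a finding does not hinge on one model form. None of this supports a claim to ensure validity, which goes beyond exploration and names small numbers as the problem overcome.

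**Conclusion.** The assurance is wrong as written, whatever the number of conditions: re-use of the same residents and largely the same ratings cannot ensure valid results. This part needs no simulation.

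The size of the further problem is conditional on how many elements enter. For an outcome unrelated to any of them, contradiction-free rows would hold about 84–99% of residents with all 15 elements, roughly 60–87% with the nine repeatedly measured ones, and about 11% or less with four or five in the full sample. These figures rest on assumed condition prevalences of 30–50%, correlation of 0–0.3 for the 15-element case and independence otherwise, and an evenly split outcome. A less common outcome or analysis within one country raises the small-k figures.

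**What to change.** - Delete the claim that the approach ensures valid results. State instead that csQCA is exploratory, uses the same data as the quantitative analyses, and that agreement between them is not independent confirmation.
- Limit each csQCA solution to a small set of conditions named in advance, about five.
- Rerun each csQCA with the QUALIDEM outcome permuted across residents, and report the observed solution against that benchmark. The benchmark takes account of the actual prevalences, correlations and outcome split, so it does not depend on the assumptions used above.

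The cost is a changed sentence, a short extra run, and fewer elements in any one solution. No data collection changes.

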## Discussion

This study will provide an insight into determinants of quality of life for people with dementia living in traditional and small-scale long-term care settings in Belgium and the Netherlands. Due to ethical considerations, a randomised controlled trial is impossible. Although they have been selected based on their similar view of care giving, the small-scale and traditional wards in the two countries are not entirely comparable. This could potentially influence the results of the study. There are differences in legislation as well as in the organization and implementation of residential care between both countries.

Moreover, the settings are real-life care settings and have specific characteristics that may vary within and between countries. The analyses will therefore be controlled for relevant differences between and within countries, such as group size, differences in the length of existence of the small-scale living facilities (ranging from September 2006 to December 2007) and differences in nursing staff, and for significant variations in the basic data of the residents.

Due to the age and frailty of the participants and the fact that the study will be conducted over the course of an entire year, there will be drop-outs, mainly due to death or occasionally to residents being moved to another institution.

Despite these limitations, collecting data from residents on various different elements, in different countries and different types of ward provides added value, because of the learning aspects and because it may enable certain patterns in the data to be discerned more clearly.

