### Small-scale living facilities and traditional care wards

Small-scale living facilities and traditional institutional psychogeriatric wards will be compared, based on the numerous differences between these two types of settings and the assumption that there will be a concomitant difference in the quality of life of the residents. Five long-term care settings have been selected for the study, of which two have traditional care wards and four have small-scale living wards: one of the settings has both small-scale and traditional wards. The long-term care settings were selected in advance, taking into account the comparability of the frailty of the residents. All residents willing to participate will be included in this study. An overview of the settings can be found in Table 1.

**Table 1 T1:** Wards

Country	Long-term care setting	Small-scale wards N	Traditional wards N	Total at T0 N
*The Netherlands*	*A*	13	51	64

	*B*	24		24

	*C*	14		14

*Belgium*	*D*	47		47

	*E*		30	30

**Total N**		**98**	**81**	**179**

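### Facility age is given for small-scale facilities only, so it cannot adjust the comparison with traditional wards; residents' length of stay, which could, is on no list of recorded data

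*Protocol article*

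**What the plan says.** The Discussion accepts that the wards are not fully comparable and commits to adjustment: "The analyses will therefore be controlled for relevant differences between and within countries, such as group size". The examples that follow include "differences in the length of existence of the small-scale living facilities (ranging from September 2006 to December 2007", then nursing staff, "and for significant variations in the basic data of the residents".

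The Analyses section makes small-scale versus traditional within each country a central comparison, and the stated null hypothesis concerns equal patterns of change on the Qualidem subscales in the two types of setting. The same section also plans Dutch versus Belgian comparisons within each ward type.

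On enrolment, the section on small-scale facilities and traditional wards says: "All residents willing to participate will be included in this study". These are people already admitted.

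On what is recorded:
- The Background list opens "The relevant elements taken into account in this study are country (the Netherlands or Belgium), type of ward (traditional or small-scale), group size" and names 15 elements.
- Environmental characteristics covers country, ward type and group size, "and nursing staff (staffing levels of qualified nurses and of other assistant staff) are recorded".
- Demographic data states that "their age and sex will be recorded at T0".
- Table 2 is presented as the overview of measurements and records.

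None of these contains an admission date or a length of stay.

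**The concern.** An adjustment variable has to take values in both groups being compared. As described, facility age has values in one group only, so it adds nothing usable to the ward-type contrast and may damage it, depending on how it is coded.

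The resident-level quantity behind facility age is time on the ward. Residents of a recently opened facility cannot have lived there longer than it has existed, whereas nothing in the article limits stay on a traditional ward in the same way. Several Qualidem subscales, such as Feeling at home, Caregiver relationship and Social relations, could plausibly depend on time since moving in. Settings are not randomised, so measured covariates are the main protection. If stay differs between ward types and is not recorded, its effect cannot be separated from that of ward type.

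**Working it through.** The plan attaches no calculation to this point, so the check concerns what the covariate can do with the numbers in Table 1.

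**Inputs.** Small-scale: A 13, B 24, C 14 (Netherlands), D 47 (Belgium); 13 + 24 + 14 + 47 = 98. Traditional: A 51 (Netherlands), E 30 (Belgium); 51 + 30 = 81. Total 98 + 81 = 179, as stated. Opening dates: September 2006 to December 2007 (Discussion). Ethics approval: September 2008. The T0 date is not given, and opening dates are not assigned to individual facilities.

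**1. Covariate left missing for traditional wards.** A complete-case model keeps 98 small-scale and 0 traditional residents. Ward type cannot be estimated.

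**2. Covariate coded 0, Belgium (D versus E, n = 47 + 30 = 77).** If D has one opening date, facility age equals that constant times the ward-type indicator. The design matrix (intercept, ward type, age) has rank 2 for 3 columns, so the two effects are fully aliased.

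**3. Covariate coded 0, Netherlands (n = 51 + 51 = 102).** The ward-type coefficient becomes the fitted small-scale mean at facility age 0 minus the traditional mean. With mean age m and within-group sum of squares S among the 51 small-scale residents, its variance relative to the model without age is

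1 + (m²/S) / (1/51 + 1/51).

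Example with assumed ages A 9, B 15, C 20 months:
- m = (13×9 + 24×15 + 14×20)/51 = 757/51 = 14.84
- S = 13×9² + 24×15² + 14×20² − 757²/51 = 816.7
- ratio = 1 + (220.3/816.7)/0.0392 = 7.9

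The ages were then varied in three-month steps from 9 to 24 months at September 2008, with both extremes present among the four small-scale settings:

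| Model | Minimum | Median | Maximum |
|---|---|---|---|
| Netherlands | 2.9 | 5.4 | 159 |
| Pooled, with country (n = 179) | 3.2 | 6.4 | 11.6 |

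**4. Any other constant.** If Dutch traditional wards are coded c and b is the slope on age within small-scale wards, the ward-type estimate is the raw difference plus b(c − m). At c = m it is exactly the unadjusted difference, with variance ratio 1. The result is therefore set by an arbitrary code and not by data on traditional wards.

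**5. Cap on time on a small-scale ward.** At September 2008: 9 months (opened December 2007) to 24 months (opened September 2006). If T0 falls between October 2008 and March 2009 (assumed): 10 to 15 months in the newest and 25 to 30 in the oldest facility.

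**6. Size of any bias.** As an approximation, bias in SD units = (difference in mean stay in SD) × (correlation of stay with the outcome analysed). The documents give neither input. Purely for illustration, a difference of 0.5 to 1.0 SD and a correlation of 0.1 to 0.3 with a subscale level give 0.5 × 0.1 = 0.05 to 1.0 × 0.3 = 0.30 SD. For the tested hypothesis the correlation needed is that of stay with change over the year. If that is zero, so is the bias in change.

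**The case against.** Four arguments deserve weight.

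- **The covariate may not be meant for this contrast.** The Discussion speaks of differences between and within countries, and facility age is defined on both sides of the Dutch versus Belgian small-scale comparison. This stands: the text does not tie the variable to the ward-type contrast. But neither does it limit the variable to small-scale analyses, and the ward-type contrast is central.
- **A short list in an article does not prove that data are unavailable.** Facility opening dates are also missing from Table 2, yet the authors have them; the adjustment list is open-ended; and a fuller protocol may record admission dates. This stands as a caution. Still, the article sets out its elements and records in several places, and time on the ward is in none of them.
- **Part of the pathway is measured.** S-MMSE, Barthel Index, NPI-NH and CSDD are taken at all three times, and settings were chosen with comparable frailty in mind. This should absorb some of any effect running through dementia stage. It does not measure adaptation to a ward.
- **The cap is on time in the facility, not in institutional care.** Residents may have moved from elsewhere, and setting A has both ward types. This is correct, and is why two admission dates are needed.

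A reader might infer that traditional wards have no length of existence. They do; the article does not give it. A reader might also infer that the comparison is shown to be confounded. It is not: no stay data are reported for either ward type.

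**Conclusion.** The point holds in limited form. As described, facility age cannot adjust the small-scale versus traditional contrast. That follows from its being given for one group only and needs no assumption beyond a single opening date for D in the Belgian case. The variance ratios rest on assumed facility ages and 0-coding.

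The contrast is open to confounding by time on the ward, because opening dates bound stay on one side and no list of recorded data includes stay. The size is unknown. It would be wrong to read the illustrative 0.05 to 0.30 SD (0.05/0.50 = 10% to 0.30/0.50 = 60% of the design effect) as the expected bias: every input is assumed, and it concerns subscale level, whereas the null hypothesis concerns change. A stable difference in level would leave that test unaffected. The planned cross-sectional analyses have no such protection.

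The change is worth making before T0 data are closed, because admission dates are cheap to collect and no other listed variable replaces them.

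**What to change.** 1. At T0, take from each resident's dossier the date of admission to the institution and the date of admission to the current ward.
2. Report length of stay by ward type within each country.
3. Include time on the current ward as a covariate in the small-scale versus traditional comparisons, for level and for change over time.
4. Check overlap of stay between ward types. Where it is limited, add a sensitivity analysis restricted to the shared range, so that the adjustment does not rest on extrapolation.
5. State that facility age is used only in comparisons among small-scale facilities. In Dutch versus Belgian small-scale comparisons, note that Belgium contributes one setting, so facility age there cannot be separated from that setting.

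The cost is two dates per resident, from records already consulted for weight, restraints and medication, and one more covariate. Precision will fall where stay overlaps little between ward types, and the restricted analysis will use fewer residents.
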